# A single-center, single-blinded, randomized, parallel-group, non-inferiority trial to compare the efficacy of a 22-gauge needle versus a 15 blade to perform an Achilles tendon tenotomy in 244 clubfeet—study protocol

**DOI:** 10.1186/s13063-023-07728-9

**Published:** 2023-10-31

**Keywords:** Clubfoot, Global surgery, Pediatrics, Orthopedics, Ponseti treatment

## Abstract

**Background:**

Achilles tendon tenotomy is an integral part of the Ponseti method, aimed at correcting residual equinus and lack of dorsiflexion after correction of the adductus deformity in clubfoot. Percutaneous tenotomy using a number 15 scalpel blade is considered the gold standard, resulting in excellent results with minimal complications. The use of a large-bore needle to perform Achilles tendon tenotomies has been described in literature, but a large-scale randomized controlled trial is currently lacking. In this trial, we aim to show the non-inferiority of the needle tenotomy technique compared to the gold standard blade tenotomy technique.

**Methods:**

We will randomize 244 feet into group A: needle tenotomy or group B: blade tenotomy. Randomization will be done using a block randomization with random block sizes and applying a 1:1 allocation to achieve an intervention and control group of the exact same size. Children will be evaluated at 3 weeks and 3 months post-tenotomy for primary and secondary clinical outcomes. The primary clinical outcome will be the range of dorsiflexion obtained the secondary clinical outcomes will be frequency of minor and major complications and Pirani score. The non-inferiority margin was set at 4°, and thus, the null hypothesis of inferiority of the needle technique will be rejected if the mean difference between both techniques is less than 4°. The statistical analysis will use a multi-level mixed effects linear regression model for the primary outcomes and a multi-level mixed effects logistic regression model for the secondary clinical outcomes. The physician performing the evaluations post-tenotomy will be the only one blinded to group allocation.

**Trial registration:**

This trial was registered prospectively with ClinicalTrials.gov registration number: NCT04897100 on 21 May 2021.

**Supplementary Information:**

The online version contains supplementary material available at 10.1186/s13063-023-07728-9.

## Introduction

### Background and rationale

#### Background

Achilles tendon tenotomy is an integral part of the Ponseti method, aimed at correcting residual equinus and lack of dorsiflexion after correction of the adductus deformity in clubfoot [1]. Achilles tendon tenotomy is required in 70–80% of all patients after a full cycle of castings has been completed [1, 2]. Percutaneous tenotomy using a number 15 scalpel blade is the gold standard, which can be performed in an outpatient setting under local anesthesia [1, 3]. A complication rate of 2% (predominantly neurovascular injuries) has been reported in literature, with accidental sectioning of the peroneal artery being the most common complication [4]. Development of a pseudo-aneurysm after accidental sectioning of the peroneal artery has been reported in a case report; which delayed further clubfoot treatment [5]. Blade tenotomy is a highly successful technique to correct insufficient dorsiflexion in clubfoot patients with about 4% of patients who do not reach the required 15° dorsiflexion, 1 year after the tenotomy requiring a re-tenotomy [1, 6, 7].

Severity of the clubfoot deformity and clinical progress in treatment of the clubfoot using the Ponseti technique can be evaluated with the Pirani score. The Pirani score is a clinical score consisting of a clinical evaluation of midfoot contracture and hindfoot contracture severity. Total score lays between 0 and 6 with 6 representing a severely malformed foot and 0 a normally appearing foot [8].

Percutaneous needle tenotomy is an established technique in orthopedics and has been described as a safe intervention for multiple purposes, including Achilles tendon tenotomy [9–12]. It is used for quadriceps tendon tenotomy in congentinal knee dislocation in newborns [9] and for superficial tendon tenotmies, in stroke patients with muscle contractures [10] among others. No contraindications have been reported for this technique in the literature [9–11].

Percutaneous needle tenotomy has been widely described in literature as an alternative technique to the blade tenotomy with very favorable results in a population before walking age [11–15]. The original technique described by Minkowitz et al. uses a large-gauge (16–19 G) needle to percutaneously cut the Achilles tendon [12, 15]. We adapted the technique for use in a low-resource setting using a 22-gauge needle [16]. Although bleeding has been reported following this technique with similar rates as for the percutaneous blade technique, no major complications have been reported in the literature as yet [12, 15]. The needle tenotomy technique is easy to use and easy to teach to clinicians who are new to the Ponseti treatment and shown to instill less anxiety in parents and caregivers compared to a blade tenotomy [15].

Inaccessibility of Ponseti clubfoot care and non-adherence to the Ponseti protocol remain big challenges in low- and middle-income countries [17, 18]. Lack of providers, long distance to clinics, and parental fear for the tenotomy are major underlying issues generating lack of access to Ponseti care [15, 17, 18]. Introducing needle tenotomies in areas with a low density of orthopedic providers by training non-surgeons to perform the tenotomy may be a gamechanger in making Ponseti care more accessible throughout the world.

The majority of reports on the needle tenotomy technique constitute case series without an active comparator [11]. To date, only one small randomized control trial comparing percutaneous needle versus blade tenotomy has been published including 55 feet [13]. The authors did not find any significant statistical difference between the two groups (*p* > 0.05). No information detailing achieved dorsiflexion post-tenotomy, the demographics of the included participants, how the sample size was determined, nor the randomization strategy were reported. A correctly sampled non-inferiority trial comparing needle tenotomy and blade tenotomy is necessary to establish the non-inferiority of the needle tenotomy to assure that introducing this technique around the globe is safe, ethical, and effective.

#### Rationale

The Ponseti method has become the gold standard treatment for clubfoot globally. It involves an Achilles tendon tenotomy in most patients, which is usually done with a blade in the majority of settings. In low-resource settings, a needle tenotomy has shown to be a technique easy to teach, with little complications and a good acceptance rate among parents and caregivers. By showing the non-inferiority of the needle technique compared to the blade technique in terms of complications and dorsiflexion range post-tenotomy, we hope to increase the technique’s usage among Ponseti providers, especially so in settings where the Ponseti treatment is provided by non-orthopedic surgeons or non-physicians, and increase access to clubfoot care in low-resource settings.

### Objectives and hypotheses

#### Objectives

Through this study, we aim to compare the clinical outcomes in children receiving either a blade or a needle percutaneous tenotomy.

*Main research questions*: Is there a difference in clinical outcome (dorsiflexion range) after an Achilles tendon tenotomy performed with a blade or needle at 3 months post-operatively?

*Secondary research questions*: Is there a difference in secondary clinical outcomes?

Secondary clinical outcomes include the following: minor and major complication frequency and types and Pirani score at 3 months post-operatively.

#### Hypotheses

*Main hypothesis*: Percutaneous needle tenotomy has a non-inferior clinical outcome compared to the use of a percutaneous blade tenotomy when comparing the patient’s dorsiflexion range.

*Secondary hypothesis*: Percutaneous needle tenotomy complication frequency and Pirani score are clinically comparable in frequency of complication (minor and major) and Pirani score to the percutaneous blade tenotomy.

## Methods

### Study setting

In order to establish non-inferiority of the needle tenotomy technique, a sufficient large enough sample size needs to be obtained. Additionally, up to 90% of children with clubfoot are born in a low- or middle-income country (LMIC), making an LMIC the culturally and environmentally most appropriate setting to generalize results beyond our center. Given the high volume of children with clubfoot who receive treatment at the Pehla Qadam clubfoot clinic at the Indus Hospital & Health Network, this center was selected for the implementation of this trial. The trial is being conducted at Pehla Qadam clubfoot clinic, The Indus Hospital, Korangi campus, Karachi, Pakistan.

### Trial design

This trial is designed as a randomized, controlled, single-blinded, single-center non-inferiority trial with two parallel groups and a primary endpoint of achieved dorsiflexion at 3 months after tenotomy. Randomization will be performed as block randomization with a 1:1 allocation.

### Patient timeline

Patients enrolled in this trial are not required to attend any additional visits beyond the visits required as part of the standard treatment protocol at Pehla Qadam clubfoot clinic. Randomization will happen at the moment the indication for an Achilles tendon tenotomy is set. The patient timeline is visualized in Fig. 1 using a SPIRIT chart and in Fig. 2 using a process flow chart.

**Fig. 1 Fig1:**
[figure not shown]
SPIRIT figure trial overview

**Fig. 2 Fig2:**
[figure not shown]
Trial process flow chart

### Consent or assent

#### Obtaining informed consent

The program coordinator for the Pehla Qadam clubfoot clinic is also the program coordinator for this trial. She evaluates patients’ eligibility into the Pehla Qadam clubfoot program during their first appointment at the clinic. If they are eligible to be enrolled as patients, the program coordinator will inform them about the ongoing studies and trials at the Pehla Qadam clubfoot clinic and inform them for which studies they are currently eligible or could potentially become eligible in the future.

If the clinical need for an Achilles tendon tenotomy is established by the treating physician, the program coordinator is informed of this potential candidate for the trial. The child’s parents/caregiver will be invited by the program coordinator to discuss the trial and potential enrollment. After eligibility for the trial is confirmed and an informed discussion has taken place, the program coordinator will obtain informed consent from the parents/caregiver and the child will receive its tenotomy the same day. The information sheet and the informed consent form will be read out loud by the program coordinator during the informed consent taking to assure that parents/caregivers have understood everything in the document before signing it. A copy of the information sheet and informed consent form are available in English and in Urdu and will be provided to the parents/caregiver. The English version of the information sheet and informed consent form is available in Additional file 1.

### Eligibility criteria

All patients under the age of 36 months where the treating physician has established the clinical need for an Achilles tendon tenotomy will be considered for inclusion. The decision to propose an Achilles tendon tenotomy to a patient has to happen in the best interest of the patient and can never be influenced by a demand of the study investigator.

Inclusion criteriaParental consent to enroll child in the studyIdiopathic clubfootAge less than or equal to 36 months at the time of tenotomyEnrolled at the Pehla Qadam clinic at The Indus Hospital in KarachiFully corrected adductus and equinus deformity after serial castingInsufficient degree of dorsiflexion (< 15°)

Exclusion criteriaRefusal of parents to enroll child into this studySyndromic clubfootPrevious treatment for clubfoot (surgical or non-surgical) receivedUnderlying medical conditions unrelated to clubfoot that may serve as a contra-indication; this decision will be left on the discretion of the treating orthopedic surgeon

### Sample size

#### Change of sample size after initial protocol creation

The sample size for this trial has been adapted after submission of the initial protocol. In preparation of submission of the final protocol for publication, it was brought to our attention that a sample size calculation for a non-inferiority trial requires the determination of a non-inferiority margin. The initial sample size, which had been calculated based on an expected difference in success rate between both tenotomy techniques, has been abandoned and replaced by a sample size calculation based on the calculation of an inferiority margin. The full calculation can be found below.

#### Non-inferiority margin determination

Dorsiflexion was defined as “true dorsiflexion” at the ankle joint and not mobility at the midfoot level. True maximal dorsiflexion measures the tibiocalcaneal angle when the foot is put in maximum dorsiflexion. Only a limited number of studies report on the range of dorsiflexion achieved after tenotomy. We identified two studies that used post-tenotomy radiographs to assess for dorsiflexion range [19, 20]. One study assessed evolution of ankle dorsiflexion over time post-tenotomy. The study states that children who still maintained 15° dorsiflexion at age 12 all had a minimum of 20° dorsiflexion under the age of 3 years [21]. This raises the question if the ideal dorsiflexion under the age of 3 years should be 20° instead of 15° as initially proposed by Ponseti. We identified 17.5° dorsiflexion, mid-way between both proposed cut-offs, minimally acceptable range of post-operative dorsiflexion in our study.

The mean range of dorsiflexion and standard deviation including the data of both radiologic studies mentioned above was determined using an inverse-variance model with random effects (Fig. 3). The obtained mean range was 21.42° of dorsiflexion. The mean range of dorsiflexion obtained from the literature is very close to the mean range of dorsiflexion (20.2°) obtained in our pilot study before starting the full RCT.

**Fig. 3 Fig3:**
[figure not shown]
Inverse-variance model with random effects to determine mean dorsiflexion rate using blade tenotomy

$$\begin{array}{c}\mathrm{Non}-\mathrm{inferiority \,margin}\\ =\mathrm{ mean \,range \,of\, dorsiflexion \,from\, literature }-\mathrm{ minimally\, acceptable\, range\, of\, post}-\mathrm{operative\, dorsiflexion}\\ = 21.42^\circ - 17.5^\circ \\ = 3.92^\circ \end{array}$$

For practical purposes, a non-inferiority margin of 4° will be applied instead of 3.92.

#### Sample size and power calculation

Sample sizes are calculated using the WHO sample size determination software [22].

Sample size calculation for primary outcome:Alpha = 5%Power 95%Non-inferiority margin: 4Standard deviation: 9.02

Required sample size = 222 feet (111 in each arm).

Drop-out from clubfoot programs is a common event in LMICs, especially throughout the bracing phase. In literature, drop-out rates of up to 30% have been reported over the total period of bracing which is about 3 years on average [17, 18, 23]. Internal data from the Pehla Qadam clubfoot program shows similar outcome with about 30% drop-out over the entire course of the treatment. We therefore expect during the first year of follow-up to lose about 10% of our patients. We will therefore increase the sample size by 10% to adjust for the expected drop-out.

A total sample size of 244 feet (122 per arm) will be recruited for this trial.

### Outcomes

Patients will be followed as per the standard follow-up schedule at the Pehla Qadam clubfoot clinic. Patients will be evaluated at 3 weeks and at 3 months post-tenotomy during regular follow-up consultations. The dorsiflexion range at 3 months post-tenotomy is considered the primary outcome. These measurement points were chosen as they coincide with the standard follow-up appointments established at the Pehla Qadam clubfoot clinic. Given that long-term follow-up is challenging in low-resource settings, the primary outcome measure was the first follow-up visit after cast removal, i.e., 3 months post-tenotomy to minimize drop-out from the trial.

The primary outcome measure is as follows: range of dorsiflexion will be registered at both follow-up visits.

The secondary outcome measures are as follows: complications including neurovascular damage in the heel region, skin, and wound problems or infections will be recorded at both follow-up visits. Neurovascular damage, an infection requiring antibiotic treatment or any other type of complication that requires the consultation of another medical specialty, will be considered a major complication. Scar hypertrophy, local edema, or erythema will be considered minor complications.

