**Secondary outcomes**			
Pirani score at 3 weeks post-tenotomy	Equal score	Pirani score with 0.5-point increments	Multi-level mixed effects linear regression
Pirani score at 3 months post-tenotomy	Equal score	Pirani score with 0.5-point increments	Multi-level mixed effects linear regression
Minor complications at 3 weeks post-tenotomy	Equal count	Number of minor complications	Multi-level mixed effects logistic regression
Minor complications at 3 months post-tenotomy	Equal count	Number of minor complications	Multi-level mixed effects logistic regression
Major complications at 3 weeks post-tenotomy	Equal count	Number of major complications	Multi-level mixed effects logistic regression
Major complications at 3 months post-tenotomy	Equal count	Number of major complications	Multi-level mixed effects logistic regression
*Complication subgroup analysis*	*Equal count*	*Number of specific type of complications*	Multi-level mixed effects logistic regression

Non-inferiority will be established if the confidence interval for the needle group does not cross the non-inferiority margin. In practice, this means a confidence interval including only values < 4. If the confidence interval includes the value 4, the trial will be determined inconclusive. If the confidence interval only values > 4, the needle tenotomy technique will be considered inferior to the blade technique.

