### Harms and adverse events

Data on adverse events will be collected from the moment the patient enrolls in the trial. In case an adverse event takes place before the tenotomy has taken place, the adverse event will be recorded as “unrelated to trial.” If an adverse event takes places after the tenotomy has taken place, it will be recorded and examined for potential causality to the trial intervention. An adverse event that meets the criteria of a “serious adverse event” will be reported to the IRB for further evaluation. A serious adverse event is defined as a life-threatening condition, a condition inflicting severe or permanent disability or needing an additional surgical intervention beyond the standard treatment plan. Serious adverse events happening after the 12-month follow-up meeting will not be reported to the IRB unless the treating physician or the program coordinator suspects a causal relationship between the trial and the adverse event.

The study team will monitor for the following tenotomy-related adverse events: excessive bleeding, neurovascular damage, infection requiring antibiotic treatment, necessity to reperform the tenotomy after 3 weeks because of incomplete sectioning of the Achilles tendon.

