## Trial summary

### Trial registration summary

A summary of the trial and its registration information can be found in Table 2.

**Table 2 Tab2:** Trial summary

Data category	Information
Primary registry and trial identifying number	ClinicalTrials.gov NCT04897100
Date of registration in primary registry	May 21, 2021
Secondary identifying numbers	N/A
Source(s) of monetary or material support	The Indus Hospital & Health Network, Karachi, Pakistan
Primary sponsor	The Indus Hospital & Health Network, Karachi, Pakistan
Secondary sponsor	N/A
Contact for public queries	[name], [contact]
Contact for scientific queries	[name] [name], The Indus Hospital & Health Network, Karachi, Pakistan [contact] [name], Université Libre de Bruxelles, Brussels, Belgium, [contact]
Public title	Outcome and Complications After Percutaneous Needle Versus Blade Achilles Tenotomy in Clubfoot Treated With the Ponseti Method
Scientific title	A single-center, single-blinded, randomized, parallel-group, non-inferiority trial to compare the efficacy of a 22-gauge needle versus a 15 blade to perform an Achilles tendon tenotomy in 244 clubfeet – study protocol
Countries of recruitment	Pakistan
Health condition(s) or problem(s) studied	Clubfoot; Achilles tendon tenotomy
Intervention(s)	Treatment group A: Achilles tendon tenotomy with 22-gauge needle Treatment group B: Achilles tendon tenotomy with 15 blade
Key inclusion and exclusion criteria	Ages eligible for study: < 36 months Sexes eligible for study: both Accepts healthy volunteers: no Inclusion criteria: Idiopathic clubfoot requiring Achilles tendon tenotomy after a full casting cycle Exclusion criteria: syndromic clubfoot, prior treatment for clubfoot
Study type	Interventional Allocation: block randomization with a 1:1 allocation Intervention model: parallel assignment Masking: Single-blinded study. Data collectors during follow-up are unaware of which intervention the patient received Primary purpose: improve treatment Phase IV
Date of first enrolment	21 May 2021
Target sample size	244 feet
Recruitment status	Recruiting
Primary outcome(s)	Degrees of dorsiflexion at 3 weeks and 3 months post-tenotomy
Key secondary outcomes	Minor and major complications at time of tenotomy, 3 weeks and 3 months post-tenotomy

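### Complication outcome: bleeding and repeat tenotomy have no clear place in the analysed comparison, the model does not match the measure, and no margin supports non-inferiority on complications

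*Protocol article*

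**What the plan says.** All references are to the protocol article.

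- **Rationale.** The stated route to wider use of the technique is: "By showing the non-inferiority of the needle technique compared to the blade technique in terms of complications and dorsiflexion range post-tenotomy".
- **Hypotheses.** The formal secondary hypothesis is weaker. Complications and Pirani score "are clinically comparable in frequency of complication (minor and major) and Pirani score to the percutaneous blade tenotomy". No margin or decision rule is attached.
- **Methods, Outcomes.** Neurovascular damage, "skin, and wound problems or infections will be recorded at both follow-up visits". Beyond neurovascular damage and infection treated with antibiotics, "any other type of complication that requires the consultation of another medical specialty, will be considered a major complication". For the minor class: "Scar hypertrophy, local edema, or erythema will be considered minor complications".
- **Harms and adverse events.** Tenotomy-related events to be monitored include excessive bleeding and "necessity to reperform the tenotomy after 3 weeks because of incomplete sectioning of the Achilles tendon".
- **Table 2 (Trial registration summary).** Key secondary outcomes are "Minor and major complications at time of tenotomy, 3 weeks and 3 months post-tenotomy".
- **Table 1.** There are rows for 3 weeks and 3 months only. The measure for the major class is "Number of major complications", the hypothesis is one of equal counts, and the method is multi-level mixed-effects logistic regression. A further row covers specific types of complication with the same model.
- **Data analysis and statistical methods, Outcomes.** Logistic regression is for binary variables, and one-tailed p-values are used throughout.

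**The concern.** Three parts of the article describe the complication outcome differently. Bleeding and incomplete section bear directly on how a tendon is cut, and both are named as tenotomy-related harms. Neither is named in the major or minor definition, and the time-of-tenotomy assessment in Table 2 has no row in Table 1. An analyst who follows Table 1 could leave these events out of the comparison between arms.

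The planned analysis adds two difficulties. A count compared under a hypothesis of equal counts is not a binary variable, so the measure and the model do not match. And events are likely to be few, so a random-effects logistic model with a one-tailed p-value would say little. The risk is that a non-significant result is read as evidence that the techniques are comparable, or as the non-inferiority on complications that the Rationale hopes to show. The article intends the results to support roll-out, including by providers who are not surgeons, so the safety statement should be one the data can carry.

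**Working it through.** **1. The plan's own figure.** The only sample size is for dorsiflexion: margin 4°, SD 9.02°, alpha 5%, power 95%. With one-sided alpha, n per arm = 2 × [9.02 × (1.645 + 1.645) / 4]² = 110.06, so 111 per arm and 222 feet. This matches, and 222 × 1.10 = 244.2 gives the 244 feet recruited (122 per arm). No figure is given for complications.

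**2. Definitions side by side.**

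| Event | Methods, Outcomes | Harms section | Table 1 row |
|---|---|---|---|
| Bleed managed in clinic | not named | named as excessive bleeding | none by name |
| Repeat tenotomy for incomplete section | not named | named | none by name |
| Complication at time of tenotomy | not mentioned (Table 2 only) | adverse events collected from enrolment | none |

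A bleed enters the major class only if it counts as neurovascular damage or needs another specialty. A repeat tenotomy by the same orthopedic team meets neither definition.

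**3. Expected events.** The Background cites a 2% complication rate, mostly neurovascular. I use it for major complications in both arms and treat feet as independent.

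- Events per arm: 111 × 0.02 = 2.2; 122 × 0.02 = 2.4. Total: 4.4 to 4.9.
- P(no event in one given arm): 0.98^111 = 0.106; 0.98^122 = 0.085.
- P(at least one empty arm) = 1 − (1 − 0.106)² = 0.20; 1 − (1 − 0.085)² = 0.16.

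With events in one arm only, the logistic odds ratio has no finite maximum-likelihood estimate; with none in either, it cannot be estimated. With four or five events in all and at most two feet per child, the variance of the child effect is barely identifiable. Analysis by visit and by type thins the data further.

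**4. Precision.** The 95% half-width for a risk difference is 1.96 × √(2 × 0.02 × 0.98 / n): 0.037 for n = 111 and 0.035 for n = 122. If 2% were observed in both arms, the upper limit would be 3.5 to 3.7 points above the blade rate, so close to a tripling would not be excluded.

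**5. What a margin would require.** The protocol gives none, so these are assumptions: 2% in both arms, one-sided 5%, 80% power, n = 2 × 0.02 × 0.98 × (1.645 + 0.842)² / margin².

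| Assumed margin (points) | Feet per arm |
|---|---|
| 2 | 606 |
| 3 | 270 |
| 4 | 152 |
| 5 | 97 |

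With 111 feet per arm, the smallest testable margin is about 4.7 points, more than twice the cited rate.

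**6. Sensitivity to the rate (assumed values).** At 1%, the chance of at least one empty arm is 50 to 55%. At 4%, which a broader definition might approach, it is 1 to 2%, but the half-width grows to about 4.9 to 5.2 points.

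**The case against.** Much can be said for the plan. The list of complications is introduced as open-ended, the major class has a catch-all, and arterial bleeding may count as neurovascular damage. Table 1 has a row for specific complication types. Both events are collected as adverse events, and an unplanned repeat tenotomy might also meet the definition of a serious adverse event. All this stands: the gap lies in the classification and analysis of these events, not in their collection. It does not give a bleed managed in clinic or a repeat tenotomy a class, and it does not add the time-of-tenotomy row.

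The count wording may simply mean the number of feet with a complication, and handling of sparse data is often left to an analysis plan. The first is easily settled by one phrase. The second does not help here, because the article itself fixes the model.

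A secondary safety outcome without a margin or power is normal, and the Rationale sentence expresses a hope. The Abstract and Discussion define non-inferiority by dorsiflexion alone. That makes the Rationale wording an overstatement to correct, not a failed primary objective.

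Three stronger readings are tempting but not supported:

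- **That these failures are particular to the needle and would be undercounted in that arm.** The Background reports similar bleeding rates with both techniques and ties its re-tenotomy figure of about 4% to the blade. No direction of bias can be claimed.
- **That the logistic model would usually give no estimate.** At 2%, both arms have events about 80% of the time.
- **That a re-cut foot enters the 3-month primary outcome with its improved dorsiflexion.** The Emergency unblinding section lets the surgeon remove a child from the trial, so the handling is open. Keeping the observed value is a recognised intention-to-treat choice, and 3-week dorsiflexion is analysed anyway.

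**Conclusion.** The point holds as a defect in how the complication outcome is defined, modelled and described. The Methods, Table 1, Table 2 and the harms section do not agree on which events count and when, so bleeding and repeat tenotomy may be left out of the comparison. The stated model does not fit the stated measure and is poorly suited to about 2.2 to 2.4 events per arm. A risk-difference interval of about ±3.5 to 3.7 points means that a non-significant one-tailed p-value cannot show comparability. The only margin, 4° of dorsiflexion, cannot be applied to a complication frequency.

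Power depends on the test: for an assumed 2% versus 6%, it is about 29% by Fisher's exact test (110 per arm, one-sided 5%) and 45% by a normal approximation (111 per arm). Either is too low to support reassurance.

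The figures rest on the cited 2% rate, taken as equal in both arms, and on independent feet. They do not cover minor complications, for which the article quotes no rate. The dorsiflexion sample size is unaffected.

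**What to change.** 1. Reconcile the Methods definition, Table 1, Table 2 and the harms section, so that excessive bleeding and repeat tenotomy, including events at the time of tenotomy, are counted in the analysed complication outcome with a stated class, and Table 1 covers that time point.
2. Define the outcome as any complication per foot (yes or no), separately for major and minor. Report the risk difference with a two-sided 95% interval suited to sparse data and allowing for clustering by child, in place of the mixed-effects logistic model and one-tailed p-value.
3. In the Rationale, restrict non-inferiority to dorsiflexion and describe complications as reported descriptively with intervals.

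The cost is wording and a simpler analysis. The events are already monitored, so no new data and no change in sample size are needed. The safety claim becomes more modest.
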